Building on learnings from the SC4C study, we propose to evaluate a model of integrated GP-pediatric care that uses a virtual approach to integrating GP-pediatric care, with the aim of demonstrating scalability and sustainability through a more equitably available model of care. The SUSTAIN study also evaluates the renowned Sydney Child Health Program (SCHP), a modular, web-based pediatric training program that has been developed for GPs, supported through the Sydney Children’s Hospital Network (SCHN) in New South Wales (NSW), and which has not previously been robustly evaluated [22].

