### Objectives

Our primary and secondary objectives are to (1) reduce GP referrals to hospital ED and outpatient (OP) clinics for children and young people younger than 18 years and (2) improve GP pediatric care aligned with best practice (BP) guidelines, GP confidence, and increase family trust in primary care, while reducing family preference for specialist pediatrician referral.

Our implementation objective is to examine factors that help or hinder the implementation of SUSTAIN and understand factors associated with acceptability and scalability, and to assess the sustainability of the model.

Our economic objective is to assess the cost-effectiveness of SUSTAIN compared to that of standard GP care by undertaking a health economic evaluation (Table 1).

**Table 1. T1:** Trial objectives, data sources, data collection methods, and outcomes.

Primary and secondary objectives	Data sources	Methods of collection	Period of data collection	Outcomes of interest
What is the impact of SUSTAIN on GP^a^ referral to hospital OP^b^ clinics and EDs?^c^ (Primary Outcome)	Referral pop-up supported through GRHANITE technologies on GP desktop	GRHANITE data extraction of referral destination (including no referral) for each pediatric visit to participating GPs.	Collected as part of pediatric GP consults at the beginning of the control data period and throughout the intervention period.	Whether or not the GP referred the child to the hospital OP clinic or emergency department.
What is the impact of SUSTAIN on GP quality of care for common childhood conditions?	GP medical records	GRHANITE data extraction of care quality based on the measurement of the CareTrack Kids indicators.	Collected as part of pediatric GP consults at the beginning of the control data period and throughout the intervention period.	Whether or not the GP followed clinical guidelines (ie, they did not request unnecessary tests or prescriptions) for 5 common childhood conditions (ie, asthma/wheezing, bronchiolitis, constipation/abdominal pain, upper respiratory infections, and infant crying, and reflux).

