### Intervention

SUSTAIN is a 12-month-long virtual model of care offered to all consenting GPs in participating general practices. It consists of four components: (1) virtual GP-led, shared GP-pediatrician consulting sessions with patients younger than 18 years, (2) virtual pediatrician-led case discussion sessions, (3) phone/email pediatrician support, and (4) complimentary access to the internationally renowned SCHP learning platform (Figure 2).

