#### GP Quality of Care

GRHANITE will be used to extract deidentified patient-level data routinely collected on all patients younger than 18 years seen by consented GPs throughout the trial. Deidentified pediatric patient data will be limited to patient demographics, reason for visit, diagnoses, referrals, prescriptions, ordered imaging and pathology testing, and Medicare item billing. The patient-level data will be used to characterize GP pediatric visits (eg, number of children seen, gender of the children, and common diagnoses) and compare quality of care for common conditions before and after the model of care is implemented, based on the CareTrack Kids indicators [28].

A natural language processing algorithm, developed by the Computing and Information Systems at the UoM for the SC4C trial, will be used to automatically transform GP EMR clinical free text of “reason for visit” or diagnosis into structured clinical data, based on the Systematized Nomenclature of Medicine Clinical Terminology [29].

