### Statistical Analysis

We will undertake descriptive analysis to describe the GP referral rate alongside the numbers of all children seen and the numbers of children referred to OP or ED by month during the study period for each practice.

All available data from each recruited GP and family will be analyzed according to an intention-to-treat principle. For the outcomes of GP referrals identified using the GP EMR data (eg, GP referral to OP clinic or ED), we will conduct mixed effects logistic regression, fitted to data collected during the control and intervention periods. The model will include a fixed effect of group (intervention vs control) and adjust for calendar time (as a continuous variable), and random effects to allow for variation in the outcomes for 3 hierarchical levels, including GP practice, GP within each practice, and patients seen by each GP.

Secondary outcomes collected at the child consultation level will be analyzed similarly, with separate models for the 5 common childhood conditions to measure quality of care. GP survey outcomes will be analyzed using mixed effects logistic regression, again including a fixed effect for group by intervention status and calendar time, and a random effect for GP practice, GPs, and patients.

We will control for baseline levels of GP referral for each practice in the analyses, GP-level factors (eg, rurality of the practice’s location, billing type, GP gender, years of practice, and number of children patients seen per week), and patient-level sociodemographic factors (eg, age at the encounter and socioeconomic status of residence). We will also consider whether the intervention effect varies by rurality of practice and GP-level factors (eg, referring level during baseline, years of practice, and GP gender) by the inclusion of interaction terms between group (intervention vs control) and these variables in the regression models.

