## Discussion

### Principal Findings

One method to prevent rising pediatric attendance at emergency departments and OP services could be strengthening the quality of pediatric health care provided by GPs closer to where people live and by increasing family confidence in the care provided by GPs for their children. This is particularly important in rural areas of countries like Australia due to the vast geographical regions. The further primary care providers are located outside of metropolitan centers in Australia, the fewer specialist services are available [48].

A primary care workforce operating at the top of the scope of practice is key to maintaining appropriate levels of services within the health care system, regardless of location. The recently released “Unleashing the Power of our Health Workforce—a Scope of Practice Review” reports that almost all health professionals in the primary care sector in Australia face some restrictions or barriers to working at the full scope of practice [49]. The SUSTAIN model, using a virtual care platform to bring GPs and pediatricians together, has the potential to empower GPs, wherever they are located, to play a greater role across the spectrum of pediatric health care from prevention, early diagnosis, management of common problems, through to chronic disease management. For children, this could reduce the need for families to seek specialist referrals for routine issues, potentially saving health care costs and wait times and leading to better long-term health outcomes. GPs may also provide recommendations for interventions for children while they are awaiting pediatrician appointments, potentially averting negative consequences of prolonged nonintervention, such as in neurodevelopmental or behavioral conditions.

Using the same rigorous mixed methods approach as for SC4C, including a stepped wedge trial design, we will be able to conduct an impact, implementation, and economic evaluation of this integrated virtual GP-pediatrician model of care for children.

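### The quality-of-care models select visits by a condition label that the GP records after exposure, so a change in labelling could be read as a change in care

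*Protocol article*

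**What the plan says.** Table 1 (Objectives) defines the quality-of-care outcome as "Whether or not the GP followed clinical guidelines (ie, they did not request unnecessary tests or prescriptions) for 5 common childhood conditions". The GP Quality of Care section says that the extracted data will be used to "compare quality of care for common conditions before and after the model of care is implemented". It also says that an algorithm will "automatically transform GP EMR clinical free text of “reason for visit” or diagnosis into structured clinical data".

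The Statistical Analysis section applies the primary model form to this outcome, "with separate models for the 5 common childhood conditions to measure quality of care". That form is a mixed effects logistic regression with a fixed effect for intervention versus control, continuous calendar time, and random effects for practice, GP and patient. The patient-level covariates given as examples are age and area socioeconomic status.

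The GPs who write the text are the GPs who are offered the intervention. It includes shared consultations, "virtual pediatrician-led case discussion sessions", phone and email support, and access to the Sydney Child Health Program, described in the Introduction as "a modular, web-based pediatric training program that has been developed for GPs".

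**The concern.** Randomizing the switch date protects a comparison over all pediatric visits. It does not protect a comparison over a subset chosen by something recorded after the switch. Here the condition label is such a record. The same clinician makes it at the same visit as the decision to test or prescribe, so a GP's judgement of what the illness is and of what to order can move together.

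If pediatric support leads GPs to record a condition in milder or more doubtful cases, or to stop doing so, the mix of visits in the model changes. Observed concordance then changes even when no child is managed differently. More complete recording has the same effect. At stake is the reading of a declared secondary outcome. The Sustainability row of Table 1 uses the same measure, so the problem would carry into that comparison too.

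**Working it through.** The document gives no rate, effect size or power for quality of care, so there is no stated figure to reproduce. The check has two parts.

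**1. Does anything in the plan protect the denominator?**

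- *Covariates (Statistical Analysis):* the patient-level examples are sociodemographic. Severity and presenting symptom are not named.
- *Sensitivity analyses (Statistical Analysis):* correlation structure, missing data, start date, compliance and contamination. None concerns who receives a label.
- *Description by month (Statistical Analysis):* children seen and children referred, not condition frequency.
- *Description of common diagnoses (GP Quality of Care):* planned to characterize visits, with no stated link to period or to interpretation.
- *Limitations:* notes that extracted data may be incomplete, not that recording may differ by intervention status.
- *Condition groups:* Table 1 pairs a symptom with a diagnosis in some groups, such as asthma/wheezing and constipation/abdominal pain. This absorbs relabelling within a group. It does not absorb movement between groups (bronchiolitis and asthma/wheezing are modelled separately) or in and out of the five. Table 2 lists asthma and constipation without the paired symptom, so even the breadth of these groups is not settled.

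**2. How large could the effect be with care held fixed?**

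All inputs here are assumptions. Split labelled visits into core cases with concordance a and borderline cases with concordance b, and let s be the borderline share. Observed concordance is (1 - s)a + sb. If only s changes, from s0 to s1, the apparent effect is (s1 - s0)(b - a).

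- a = 80%, b = 50%, s from 20% to 10%: 0.8×0.80 + 0.2×0.50 = 74%, then 0.9×0.80 + 0.1×0.50 = 77%. Apparent gain 3 points, odds ratio (0.77/0.23)/(0.74/0.26) = 1.18.
- Same a and b, s from 20% to 30%: 74% to 71%. Apparent loss 3 points, odds ratio 0.86.
- a = 80%, b = 30%, s from 30% to 10%: 65% to 75%, odds ratio 1.62. The reverse move gives 75% to 65%, odds ratio 0.62.
- a = 70%, b = 40%, s from 20% to 10%: 64% to 67%, odds ratio 1.14.
- s unchanged, or a = b: no shift.

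Over these inputs the range is -10 to +10 points, odds ratio 0.62 to 1.62.

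A count example shows the same mechanism at an extreme. Take 50 labelled visits of which 20 are non-concordant: 20/50 = 40.0%. Adding the label to 15 further visits, all concordant, gives 20/65 = 30.8%. Removing it from 15 concordant visits gives 20/35 = 57.1%. The same 20 tests or prescriptions occur each time.

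**3. Why a check on labelling must allow for season.** Eighteen practices switching three per month from October 2023 gives 18/3 = 6 start months, October 2023 to March 2024. That agrees with a 12-month intervention ending in February 2025 for the last practices. All control data therefore fall between September 2023 and February 2024, while intervention data run through the Australian winter of 2024. A raw comparison of how often bronchiolitis or upper respiratory infection is recorded would differ by season alone.

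**The case against.** The strongest case against runs as follows.

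- *No passage says that labelling changes.* This stands. A reader might infer that the intervention teaches diagnosis and so does change who is labelled. The document supports only that it can. The phrase "across the spectrum of pediatric health care from prevention, early diagnosis, management of common problems, through to chronic disease management" comes from the Discussion and describes the role GPs might play. It is not a trial objective, and the neurodevelopmental and behavioral conditions mentioned there are not among the five.
- *A condition-specific indicator needs a condition denominator, and its construction belongs in the analysis plan.* Partly stands. The concordance models are legitimate and should remain. But the article itself fixes the outcome, the source of the label and the model, and the point concerns the consequence of that choice.
- *Coding reason for visit as well as diagnosis, and grouping symptoms with diagnoses, narrows the route.* This stands within a group, not across groups.
- *An all-visit rate of tests or prescriptions does not measure concordance.* This stands: it mixes necessary with unnecessary orders. Its denominator can also shift, because the Adoption and Fidelity section hypothesizes better access for children with greater socioeconomic need, and a poster promotes the shared consultations. It can therefore support the declared outcome but not replace it.
- *Requiring stable label frequency would fail respiratory conditions on season alone.* This stands against an unadjusted stability rule. It is met by estimating the intervention-versus-control difference with adjustment for calendar month.

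**Conclusion.** Each quality-of-care model conditions on a record that the exposed GP makes after the switch, and no analysis stated in the article addresses this. A labelling change could be read as a change in guideline concordance in either direction.

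The size is unknown. The 3-point and 10-point shifts, and the larger shifts in the count example, are illustrations under assumed rates and do not estimate bias in this trial. The bias requires two things together: that labelling responds to the intervention, and that concordance differs in the visits that move.

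A reader might infer that the quality-of-care results will be invalid, or that the trial's main secondary objective is compromised. The document supports neither. It does not rank the secondary objectives, and labelling may prove unaffected. The primary referral outcome is defined over every pediatric visit to participating GPs and is untouched. This is an inexpensive safeguard for one secondary outcome and its sustainability follow-up.

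**What to change.** Keep the five condition-specific concordance models as the declared secondary analysis. Add two supporting analyses for each condition to the analysis plan:

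1. Over all pediatric visits in the relevant age band, model whether the visit receives the label. Use the same mixed model but adjust for calendar month, since a single continuous time term cannot follow season. Report the intervention-versus-control difference with its interval.
2. As a sensitivity analysis, model the condition's target tests or prescriptions per pediatric visit over all visits in that age band.

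State in advance that if (1) shows labelling differs by intervention status, or if (2) disagrees with the condition-specific result, that result will be interpreted with caution and not presented as a change in care. A wide interval in (1) should not be taken as evidence of stable labelling.

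The cost is wording, a defined age band per condition and up to ten more models. No new data are needed, because diagnosis, prescribing, imaging and pathology fields are already extracted for every patient under 18 seen by a consented GP. The all-visit measure is diluted, mixes necessary with unnecessary orders and does not remove changes in who attends.

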What is the impact of SUSTAIN on GPs? (eg, confidence and skills in pediatric care and use of clinical guidelines)	GP web-based survey	Web-based control and intervention surveys completed by GPs via REDCap^d^.	Control surveys are collected in the month prior to the implementation commencing in each practice. Intervention surveys are collected in the last month of the implementation at each practice.	Changes in the level of confidence in pediatric care, level of knowledge and skill in navigating the health system for children, and reported use of clinical guidelines.
What is the impact of SUSTAIN on patients and family experience?	Family web-based survey	Web-based control and intervention surveys completed by families/caregivers via REDCap.	Control surveys are collected in the month prior to the implementation commencing in each practice. Intervention surveys are collected in the last month of the implementation at each practice.	Level of confidence in GP care, level of satisfaction with GP care, desire for referral to specialist care, and preference for GP or specialist review.
Health economic evaluation				
What is the cost of implementing the model of care? What is the cost- effectiveness?	Trial data and supplementary unit costings	Trial data on the model of care, health service activity, and combined with relevant unit costs.	Data will be collected throughout the model of care.	Costs of conducting the model of care compared with usual care and costs/cost offsets from changes in OP/ED referrals, MBS,^e^ and PBS^f^ (including out-of-pocket fees) compared with accessing usual care.
Implementation evaluation				

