#### GP and Family Data Collection

GP and family survey data collection will occur preintervention (baseline) and in the last month of the SUSTAIN model of care (intervention) for each practice.

A web-based GP Survey (Section S3 in Multimedia Appendix 4) will be used to measure GP experience and confidence in pediatric care, completed by all participating GPs via REDCap. Based on the SC4C trial, the survey collects information including GP demographics, factors that impact their decision to refer a pediatric patient, and knowledge and confidence in pediatric care and services. GP name and general practice will be recorded for survey completion tracking, but will not be attached to the survey responses.

A web-based family survey (Section S4 in Multimedia Appendix 2) will be used to measure caregivers’ perceptions and experience of pediatric care provided at their general practice. To provide data on a “whole of practice” level, caregivers of a patient <18 years, regardless of whether they attended a consultation with a participating GP, will be eligible to complete the Family Survey via REDCap. The survey collects information on the child/family regarding a GP visit up to 3 months prior. These surveys are voluntary, and responses are anonymous.

No power calculation has been performed, as we will recruit as many families as possible during this timeframe and use all available data.

SUSTAIN GP and family surveys have been adapted from the SC4C study and comprise items generated by the SC4C investigators and drawn from previously published literature [19,30,31]. Data collection timepoints for participant enrollment and interventions can be found in Table 2.

**Table 2. T2:** Outline of participant enrollment, intervention, and data collection timepoints.

	Enrollment (–t_1_)	Allocation (t_0_)	Study period			Close out (t_x_)
			Control period (t_1_)	1-month Embedding period (t_2_)	11-month Intervention period (t_3_)	
Enrollment						
General practice eligibility screen	✓					
Informed GP^a^ consent	✓					
General practice intervention allocation		✓				
Intervention						
Virtual GP-pediatrician coconsultation				✓^b^	✓	
Virtual case discussions				✓^b^	✓	
Pediatrician phone/email support				✓^b^	✓	
GP access to SCHP^c^				✓^b^	✓	
Primary outcome						
GP referral outcomes						
GRHANITE extracted from routinely collected GP EMR^d^ data			✓	✓^b^	✓	
Secondary outcomes						
GPs						
Quality of care						

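### GP survey outcomes are defined as changes in level but assigned to logistic regression, which read plainly collapses graded items at an unstated cut; an ordinal mixed model should be named

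*Protocol article*

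**What the plan says.** In the Objectives section, Table 1 gives the outcomes for the impact on GPs as "Changes in the level of confidence in pediatric care, level of knowledge and skill in navigating the health system for children", together with self-reported use of clinical guidelines.

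On the instrument, GP and Family Data Collection says: "A web-based GP Survey (Section S3 in Multimedia Appendix 4) will be used to measure GP experience and confidence in pediatric care". That appendix is not shown, so the response options are not visible. On timing, the same section says: "GP and family survey data collection will occur preintervention (baseline) and in the last month of the SUSTAIN model of care (intervention) for each practice".

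On the model, Statistical Analysis says: "GP survey outcomes will be analyzed using mixed effects logistic regression", and continues: "again including a fixed effect for group by intervention status and calendar time, and a random effect for GP practice, GPs, and patients". For the referral outcomes, which Table 1 frames as whether or not a referral was made, the same section says: "we will conduct mixed effects logistic regression, fitted to data collected during the control and intervention periods".

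The article names no ordinal, cumulative or linear model for the GP survey. It states no dichotomisation and no cut-point.

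**The concern.** A level of confidence or skill is a graded quantity. Logistic regression without a qualifier is a model for a two-category outcome, and the section uses the term in that sense for referrals. Applied to a graded item, it estimates the odds of being above some threshold. That is a different quantity from a change in level.

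Three things follow if the plain reading is right:

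- Movement within the categories on one side of the threshold carries no weight in the estimated effect.
- The answer can change with the threshold, and none is fixed in the article.
- Information is lost where there may be little to spare. The survey goes only to participating GPs in a trial planned for 18 practices, at two time points.

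GP confidence is a named secondary objective, so a real but modest gain could be reported as not shown.

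**Working it through.** **Is there a plan figure to reproduce?** Not for this point. The only power statement in Sample Size Calculation concerns referrals (90% power for a 3.7-point reduction from 10%, plus the stratified analyses of the same outcome). As a check, a stepped wedge calculation was run with 18 practices in 6 steps of 3, 60 consultations per practice per month, intracluster correlation 0.06, 18 calendar months as categorical effects, and the embedding month dropped. It gives 89.5-91.2% for the 3.7-point reduction, depending on how the correlation is applied, so that figure reproduces. It says nothing about the GP survey, for which the article gives no sample size, effect size or power.

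**How much does one cut lose?** Because the scale is not visible, this can only be illustrated. The comparison assumes two equal independent groups, proportional odds and a small effect. It ignores clustering, pairing and calendar time.

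- Ordinal information per response, up to a common factor: (1 − Σp_k³)/3, where p_k is the share of responses in category k.
- Binary information at a cut with cumulative share c, up to the same factor: c(1 − c).
- Relative efficiency: RE = c(1 − c) / [(1 − Σp_k³)/3].
- Power of the binary analysis when the ordinal one has 80%: Φ((1.96 + 0.8416)·√RE − 1.96).

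Consistency check: with two categories, 1 − p³ − (1 − p)³ = 3p(1 − p). The ordinal formula then reduces to p(1 − p) and RE = 1, as it should.

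Worked example, five equal categories: Σp_k³ = 5 × 0.2³ = 0.04, so the ordinal information is 0.96/3 = 0.32. A cut at c = 0.4 gives 0.4 × 0.6 = 0.24 and RE = 0.24/0.32 = 0.75. Power is Φ(2.8016 × 0.866 − 1.96) = Φ(0.466) = 68%.

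| Assumed category shares | Ordinal information | RE at each cut, lowest to highest | Binary power at each cut |
|---|---|---|---|
| 0.2, 0.2, 0.2, 0.2, 0.2 | 0.320 | 0.50, 0.75, 0.75, 0.50 | 51%, 68%, 68%, 51% |
| 0.1, 0.2, 0.4, 0.2, 0.1 | 0.306 | 0.29, 0.69, 0.69, 0.29 | 33%, 64%, 64%, 33% |
| 0.03, 0.07, 0.2, 0.45, 0.25 | 0.295 | 0.10, 0.31, 0.71, 0.64 | 14%, 34%, 66%, 61% |
| 0.05, 0.25, 0.5, 0.2 | 0.284 | 0.17, 0.74, 0.56 | 21%, 67%, 56% |
| 0.2, 0.5, 0.3 | 0.280 | 0.57, 0.75 | 56%, 68% |

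The best cut in each row keeps 69-75% of the information (binary power 64-68%). The remaining cuts keep 10-64% (binary power 14-61%).

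If the outcome were instead a continuous normal score, a cut at quantile q keeps φ(z_q)²/[q(1 − q)]. That is 64% at the median (80% power falls to 61%) and 34% at a 90/10 split.

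**The case against.** The strongest objection is that neither a binary model nor a single cut is written in the article. A cumulative logit model is also a logistic regression and is not excluded. The instrument is in an appendix not shown, and item coding is commonly left to a statistical analysis plan. This stands as far as it goes: binary is the plain reading, not an express statement. It does not dispose of the point. The article does name a model, uses the same name for a yes/no outcome, and pairs it with an outcome defined as a change in level. A cut fixed later in an analysis plan would still replace that outcome with a proportion above a threshold.

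A reader might also infer stronger things that the article does not support:

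- **That GPs who improve would be scored as unchanged.** The model compares responses by intervention status and calendar time. It forms no change score and classifies no GP as improved or not.
- **That every GP survey outcome is affected.** Reported guideline use may be a yes/no item, for which binary logistic regression is suitable.
- **That a specific power loss applies to this trial.** Paired simulations can show larger gaps. One used an assumed 72 GPs, a five-level item, within-GP correlation 0.5 and a shift of 0.4 SD. A signed-rank test on all levels had 86% power, against 53% for an exact McNemar test with the cut at level 4 or above. The ordinary McNemar score test raises the 53% to 63%, so (63 − 53)/(86 − 53), about a third of the gap, comes from the conservative exact test. None of these tests is the planned model. Pairing is also uncertain. The article says "GP name and general practice will be recorded for survey completion tracking, but will not be attached to the survey responses", although the Data Management Plan gives each GP an ID code that might allow linkage. With independent samples, the same setting gave 60% against 46%.

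The direction of the loss is the same in every version; its size is not known.

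**Conclusion.** The point holds as a mismatch between the definition of the graded GP survey outcomes and the model named for them. On the plain reading, those items are reduced to two categories at a cut that the article does not give. This discards information and makes the result depend on the cut.

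For scale only: under proportional odds and the category distributions assumed above, even the best cut loses about 25-31% of the information, and poor cuts lose far more. These figures do not measure the loss in this trial, since the response scale, its distribution and the number of GPs are not stated. If a cumulative logit model was meant all along, only the wording is at fault.

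The matter affects a secondary outcome and leaves the referral analysis untouched. It is worth correcting because correction is cheap.

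**What to change.** In Statistical Analysis, split the sentence on GP survey outcomes by type of item:

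- For items recorded on a graded scale, name a mixed effects ordinal (cumulative logit) model on the full scale, with the same fixed effects for intervention status and calendar time.
- For items recorded as yes/no, possibly including reported guideline use, keep binary mixed effects logistic regression.
- Report any percentage above a cut descriptively, with the cut fixed before analysis.

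If a cumulative logit model was already intended, state that.

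The cost is a change of wording, with no new data. The one statistical price is a proportional-odds assumption, which should be checked and reported.
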